#### **6.1.2 Assessment of Severity (Intensity)**

**Mild:** awareness of a sign or symptom but patient can tolerate.

**Moderate:** discomfort enough to cause interference with normal daily activity.

**Severe:** resulting in an inability to do work or do usual daily activity.

#### **6.1.3 Assessment of Causality (WHO Definitions)**

**Definite Association:** An event that follows a reasonable temporal sequence in relation to the administration of the drug or in which the drug level has been established in body fluids or tissues, that follows a known response pattern to the suspected drug; and that is confirmed by improvement upon stopping the drug (de-challenge) and reappears on repeated exposure (re-challenge).

**Probable Association:** An event that follows a reasonable temporal sequence in relation to the administration of the drug, that follows a known response pattern to the suspected drug and that is confirmed by de-challenge; and that cannot be reasonably explained by the known characteristics of the patient's clinical state. Re-challenge information is not required to fulfill this definition.

**Possible Association:** A clinical event, including laboratory test abnormality, with a reasonable time sequence to administration of the drug, but which could also be explained by concurrent disease or other drugs or chemicals. Information on drug withdrawal may be lacking or unclear.

**Unlikely Association:** A clinical event, including laboratory test abnormality, with a temporal relationship to drug administration which makes a causal relationship improbable, and in which other drugs, chemicals or underlying disease provide plausible explanations.

Conditional Association: A clinical event, including laboratory test abnormality, reported as an adverse reaction, about which more data is essential for a proper assessment or the additional data are under examination.

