## 6 SAFETY ASSESSMENTS

### 6.1 Adverse Event/Serious Adverse Event Definition

The occurrence of adverse events (AE) will be monitored throughout all phases of the study and will cover all participating patients.

Adverse events are to be elicited by the physician (or designate) asking the patient non-leading questions. The association of the AE to VariZIG™ is to be judged by the physician as definite, probable, possible, unlikely or conditional.

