#### **6.1.4 Description of Known Adverse Event Profile for VariZIG™.**

Reactions to VariZIG™ are rare and mild in intensity. In the intended patient population, the most frequent treatment related adverse events were pain at the injection site, headache and rash. Other less frequent adverse reactions were myalgia, rigors, fatigue, nausea and flushing. The adverse event profile of VariZIG™ is expected to be comparable to other commercially available varicella zoster immune globulin (human) and intravenous immune globulin (human) products. The most common expected adverse drug reactions are chills, fever, headaches, vomiting, allergic reactions, nausea, arthralgia and moderate low back pain.

As is the case with all immune globulin drugs, there is a remote chance of an anaphylactic/anaphylactoid reaction with VariZIG™ in individuals with hypersensitivity to blood products. In the event of an immediate hypersensitivity reaction (anaphylaxis) characterized by collapse, rapid pulse, wheezing, difficulty breathing, pallor, cyanosis, edema or generalized urticaria, epinephrine should be administered followed by hydrocortisone and/or antihistamine, if necessary.

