#### **8.2.1 Primary Endpoint**

The primary endpoint of this study is the incidence of adverse events associated with VariZIG™.

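### After a single dose, the Section 6.1.3 causality definitions keep clear drug reactions out of 'probable' and 'definite', which blurs the relationship data behind the primary endpoint

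*Protocol*

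**What the plan says.** Protocol Section 8.2.1: "The primary endpoint of this study is the incidence of adverse events associated with VariZIG™". Section 6.1 says that association is "judged by the physician as definite, probable, possible, unlikely or conditional", and Section 6.1.1 requires every event to be assessed against the criteria that follow it. Section 8.3 tabulates relationship in frequency tables.

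Section 6.1.3 defines the grades:

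- **Definite.** The event must be "confirmed by improvement upon stopping the drug (de-challenge) and reappears on repeated exposure (re-challenge").
- **Probable.** The event must be one that "follows a known response pattern to the suspected drug and that is confirmed by de-challenge", with no reasonable explanation in the patient's clinical state. The text adds: "Re-challenge information is not required to fulfill this definition".
- **Possible.** The timing is reasonable, "but which could also be explained by concurrent disease or other drugs or chemicals". Withdrawal information may be missing.
- **Unlikely.** Timing makes causation improbable, and something else plausibly accounts for the event.
- **Conditional.** Further data are needed, or are being examined, before a proper assessment can be made.

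The Schedule of Events puts dosing at Visit 1 (Day 0) only. A footnote allows re-dosing on other days when clinically justified. Section 5.3 also allows additional doses and IV administration. Section 6.1.4 reports that in the intended population "the most frequent treatment related adverse events were pain at the injection site, headache and rash".

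**The concern.** De-challenge and re-challenge are evidence from a course of treatment that can be interrupted and resumed. Most patients here can be expected to receive one administration. Once it is given nothing can be withdrawn, and without a second dose nothing can reappear. A scale that makes these observations conditions of its two upper grades asks for evidence that the default patient does not generate.

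This matters because the study is open-label with no concurrent control, in immunocompromised patients, infants and pregnant women, where background events are to be expected. The investigator's grade is the main thing that separates drug effect from background. If clear reactions land in the same grade as confounded events, the relationship tables lose much of their meaning. A later analysis plan can pool grades, but it cannot recover a distinction that was never recorded.

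**Working it through.** No figure in the protocol depends on this, so there is no arithmetic to reproduce. The check takes one test event through each definition.

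**Test event.** Injection-site pain after one IM dose, with plausible timing, a known response pattern (it is named in Section 6.1.4), no other cause and no further dose.

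| Grade | Condition in 6.1.3 that decides it | Met? |
|---|---|---|
| Definite | De-challenge and re-challenge | No: nothing to stop, no second exposure |
| Probable | De-challenge; no other reasonable explanation | No on a literal reading: the second condition holds, the first cannot be assessed |
| Possible | Another explanation could apply | No: there is none |
| Unlikely | Causation improbable | No |
| Conditional | Essential data still to come or under examination | Poor fit: the missing de-challenge data will never come |

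The allowance in 'possible' for missing withdrawal information relaxes only the withdrawal evidence. It does not remove the condition that something else could explain the event. An immediate hypersensitivity reaction with no other cause, after a single completed dose, gives the same five answers.

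**With re-dosing.** Re-challenge can then be observed, so 'definite' is not ruled out on that ground. The protocol does not say how many patients will be re-dosed, so their share is unknown.

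**Consequence for the primary count.** The protocol does not state which grades make an event 'associated'. For a clear reaction in a once-dosed patient, graded literally and pushed down to 'possible' or 'conditional':

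| If 'associated' means | Effect on the primary count |
|---|---|
| Definite + probable | The event drops out |
| Definite + probable + possible | It stays if graded 'possible', drops out if graded 'conditional' |
| Definite + probable + possible + conditional | It stays; only the breakdown by grade is wrong |

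The misgrading of relationship therefore occurs under every rule. The effect on the headline incidence ranges from none to loss of the event, depending on the cut.

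**The case against.** The strongest reply has four parts.

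1. **VariZIG is not strictly single-dose here.** Re-dosing, additional doses and IV use are all allowed. This stands. Re-challenge can occur in some patients, and an IV administration might be interrupted. The point must be confined to patients dosed once, although they are the default.

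2. **Events will still be graded and counted.** Investigators would use 'possible' or 'conditional', and all events are documented (Section 6.1.1) and tabulated (Section 8.3) whatever their grade. This also stands, so the harm is down-grading and inconsistency. It is not loss of events from the safety tables.

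3. **The problem affects few event types.** Headache, rash or fever in these patients, with no restriction on concomitant medication (Section 4.3), can often be explained by something else, and 'possible' then fits. This largely stands. The gap is clearest for injection-site pain and immediate hypersensitivity, but the former is named first among the most frequent related events.

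4. **Resolution after the dose could be taken as de-challenge.** The text does not forbid this for 'probable', but it does not say it either, and under 'definite' de-challenge is explained as improvement on stopping the drug. Some sites would take that reading and others would not. With some centers joining for individual patients (Section 3.2), such inconsistency is a realistic risk.

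A reader might also infer that the primary endpoint will be zero or nearly zero by construction. The documents do not support that. It would need 'associated' to mean definite plus probable only, which no section says, and it would need no patient to be re-dosed.

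**Conclusion.** The definitions are wrong as written for the default patient. After one administration, a clear drug reaction with no other cause literally meets none of the five grades. It would be down-graded or graded inconsistently, and this distorts the relationship tables that support the primary endpoint.

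The size cannot be put as a number. The protocol gives neither the number of re-dosed patients nor the expected number of unambiguous reactions. Total adverse event counts are unaffected, taking Section 6.1.1, which documents all events, over the narrower Safety Parameters row of the synopsis, which speaks of related events. No sample size, power or test changes.

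The conclusion assumes that most patients follow the Day 0 schedule and that the definitions are applied as worded.

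Two neighbouring points do not carry this finding. The scale has no 'not related' grade, but adding one is largely preference: if 'unlikely' is not counted as associated, it would change no endpoint count. How missing grades are counted can be left to the SAP.

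**What to change.** In Section 6.1.3, state that the de-challenge and re-challenge criteria apply only where applicable. After a single administration, let the upper grades rest on timing, known response pattern and the absence of another reasonable explanation.

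In Section 8.2.1, tie 'associated' to named grades that include 'possible' and 'conditional', so that a down-graded event cannot drop out of the primary count. This second change protects the headline incidence, but it does not repair the breakdown by grade. Both changes are needed.

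The cost is protocol wording and matching wording on the electronic data forms. Counts of definite or probable events may rise, because clear reactions would be graded as such.

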#### **6.1.4 Description of Known Adverse Event Profile for VariZIG™.**

Reactions to VariZIG™ are rare and mild in intensity. In the intended patient population, the most frequent treatment related adverse events were pain at the injection site, headache and rash. Other less frequent adverse reactions were myalgia, rigors, fatigue, nausea and flushing. The adverse event profile of VariZIG™ is expected to be comparable to other commercially available varicella zoster immune globulin (human) and intravenous immune globulin (human) products. The most common expected adverse drug reactions are chills, fever, headaches, vomiting, allergic reactions, nausea, arthralgia and moderate low back pain.

As is the case with all immune globulin drugs, there is a remote chance of an anaphylactic/anaphylactoid reaction with VariZIG™ in individuals with hypersensitivity to blood products. In the event of an immediate hypersensitivity reaction (anaphylaxis) characterized by collapse, rapid pulse, wheezing, difficulty breathing, pallor, cyanosis, edema or generalized urticaria, epinephrine should be administered followed by hydrocortisone and/or antihistamine, if necessary.

#### **Clinical Trial Adverse Drug Reactions**

See the current VariZIG™ Investigator's Brochure for complete details.

#### **6.2 Adverse Event Reporting**

Occurrence of adverse events will be monitored throughout all phases of the study at all visits and will cover all participating patients. Study patients should be provided with a 24hr telephone number to contact study personnel in case of an untoward reaction. The investigator(s) should follow all adverse events to resolution.

#### **6.3 Reporting of SAEs**

The investigator (or designate) will report all serious adverse and/or unexpected events to the sponsor within 24 hours of occurrence by telephone (i.e. within 24 hours of the investigator's (or designate's) knowledge of occurrence). This will be followed by a fax of the SAE Form. A written SAE report by the investigator to the sponsor (including medical summary of the SAE) must follow within 3 days of the investigator's (or designate's) knowledge of occurrence of the SAE. Telephone reports should be made to the contact listed below.

██████████ OR  
Manager, Pharmacovigilance  
Cangene Corporation  
[name]  
[name]  
Phone: ██████████  
Fax: ██████████  
Cell: ██████████

██████████  
Safety Surveillance Officer  
Cangene Corporation  
[name]  
[name]  
Phone: ██████████  
Fax: ██████████  
Cell: ██████████

Phone: ██████████ (North America only)  
Fax: ██████████ (North America only)

## 7 STUDY MEDICATION

### 7.1 Medication Shipment

VariZIG™ is stored at ██████████. Upon the physician's request, VariZIG™ will be shipped to the physician at a temperature of 36 to 46°F (2 to 8°C). The physician or designate will be responsible for checking the number of vials and the condition of the vials received.

### 7.2 Packaging and Formulation

VariZIG™ is supplied as a kit containing one 6 mL glass vial, which contains greater than 125 IU of freeze-dried VariZIG™, fitted with butyl rubber stopper and an aluminum seal with a plastic flip-off cap. Each package also contains 8.5 mL of sterile diluent, for reconstitution of VariZIG™. Refer to Section 7.5 of this protocol and the Investigator's Brochure for further details.

The final product formulation includes addition of sodium chloride to yield 0.04 M, glycine to yield 0.1 M and polysorbate 80 to yield 0.01%. The accompanying sterile diluent contains 0.8% sodium chloride and 10 mM sodium phosphate. The reconstituted product contains no preservative.

### 7.3 Labeling

VariZIG™ vial labels will include:

- Name of drug
- Lot number
- Expiration date
- Recommended storage conditions
- Name and address of manufacturer

- Name and address of distributor

The following will also be included:

“Caution: New Drug – Limited by Federal Law to Investigational Use”

#### 7.4 Storage Conditions

Store VariZIG™ at 36 to 46°F (2 to 8°C). Do not use after expiry date. **Do not freeze.**

#### 7.5 Preparation

VariZIG™ should be brought to room temperature immediately prior to use. Following reconstitution, the product should be clear or slightly opalescent. Do not use product that appears cloudy or contains deposits.

VariZIG™ should be reconstituted only with the accompanying vial of Sterile Diluent. Use aseptic technique throughout. Reconstitute shortly before use. To reconstitute:

1. Remove caps from the diluent and product vials
2. Wipe exposed central portion of each rubber stopper with suitable disinfectant
3. Withdraw the contents of the diluent using a suitable syringe and needle. For IM administration, reconstitute using a volume of 1.25 mL sterile diluent. For IV administration, reconstitute using a volume of 2.5 mL sterile diluent. (Refer to Investigator's Brochure for further details).
4. Inject diluent slowly at an angle so that the liquid is directed onto the inside glass wall of the vial containing the freeze-dried pellet.
5. Wet pellet by gently tilting and inverting the vial. Avoid frothing. Gently swirl upright vial until dissolved (less than ten minutes). **Do not shake.**

Reconstituted product can be stored for up to 12 hours at 36 to 46°F (2 to 8°C) prior to use.

| Table 3: Reconstitution of VariZIG™ |           |                                       |                              |                              |
|-------------------------------------|-----------|---------------------------------------|------------------------------|------------------------------|
| Route of Administration             | Vial Size | Volume of Diluent to be added to vial | Approximate Available Volume | Nominal Concentration per mL |
| Intravenous (IV)                    | 6 mL      | 2.5 mL                                | 2.4 mL                       | 50 IU/mL                     |
| Intramuscular (IM)                  | 6 mL      | 1.25 mL                               | 1.2 mL                       | 100 IU/mL                    |

## **7.6 Drug Accountability**

The product supplied under this protocol is to be used solely for the treatment of the patient for which it is being released by [REDACTED] or Cangene Corporation.

The physician is responsible for submitting to [REDACTED] the necessary documents acknowledging receipt of the product, date of administration, dosage used and the indication for which it was used.

A research pharmacist or a designated individual will maintain a current inventory and ongoing record of test material supplies using the Drug Accountability Form provided by Cangene Corporation. This inventory record will include:

- Protocol name.
- Product name and description.
- Physician's name and site location.
- Product lot number.
- Number of vials dispensed, date of dispensing and patient for whom product was dispensed.
- Product balance.
- Name of qualified individual dispensing product.

These records may be reviewed by representatives of Cangene Corporation or the FDA.

## **8 STATISTICAL ISSUES IN STUDY DESIGN AND EFFICACY ASSESSMENT**

### **8.1 Sample Size**

All eligible consented patients will be enrolled in this study. There is no upper or lower limit for the number of patients enrolled. For evaluation of the secondary endpoint, a minimum of 16 immune compromised patients enrolled into this study will be compared to untreated historical control data for the incidence of pneumonia in at-risk patients exposed to VZV (chicken pox) infection. This will allow 80% power to detect a 25% difference between patients treated with VariZIG™ and historical control values.

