### **3.3 Sample Size**

This expanded access protocol is intended to provide VariZIG™ to all patients determined by their physician to be in need of this treatment, and who give their informed consent, until licensing of VariZIG™. Thus, the number of patients to be enrolled under this expanded access protocol is unknown. However, a minimum of 16 consented patients will be used in the efficacy analysis (see Section 8.1 for further details).

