### 8.3 Planned Method of Analyses

Adverse events will be coded and listed. The incidence, intensity and relationship of events to VariZIG™ will be evaluated through the use of frequency tables. Adverse events will be tabulated by body system and preferred term, both in terms of number of occurrences and in terms of number of patients affected. Serious adverse events will be listed and tabulated in a similar fashion.

As a secondary endpoint analysis, historical rates of developing pneumonia in untreated patients will be compared to the observed rates of pneumonia development in patients in at-risk groups treated with VariZIG™. The at-risk group includes immunocompromised/immunodeficient patients (Table 4). The superiority comparison will be performed using Fisher's exact test for proportions with a probability of type I error set at 0.05.

| Table 4: Historical Rate of Development of Pneumonia in At-Risk Patients
Untreated and Treated with VZIG |                                                                |                                                                        |
|---------------------------------------------------------------------------------------------------------------------|----------------------------------------------------------------|------------------------------------------------------------------------|
| Risk Group                                                                                                   | Untreated (% Development
of Pneumonia) | Treated with VZIG (%
Development of Pneumonia) |
| Immunocompromised/
Immunodeficient                                                                               | 25%                                                            | 6%                                                                     |

Descriptive statistics will be provided for the percent of patients with a pox count >100, for the incidence of mortality, pneumonia and encephalitis in at-risk patients, and for the overall incidence of infection.

Concomitant medications will be coded and classified by an appropriate drug dictionary. These categories will be tabulated and summarized. Concomitant medications will also be listed individually, in full.

Demographic and baseline characteristics will be summarized using appropriate summary statistics.

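### The 80% power claimed for 16 patients rests on an undefined 25% difference that conflicts with Table 4; at Table 4's own rates, power against a fixed 25% is about 37%

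*Protocol*

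**What the plan says.** Section 8.1 sets the size of the efficacy comparison: "a minimum of 16 immune compromised patients enrolled into this study will be compared to untreated historical control data" for pneumonia. It adds: "This will allow 80% power to detect a 25% difference between patients treated with" VariZIG and historical values. The Synopsis carries the same power sentence. Section 3.3 repeats the 16 ("a minimum of 16 consented patients will be used in the efficacy analysis") and refers to 8.1, but makes no power claim of its own.

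Section 8.3 names the test for this superiority comparison, "Fisher's exact test for proportions with a probability of type I error set at 0.05", and the risk group: "The at-risk group includes immunocompromised/immunodeficient patients (Table 4"). Table 4 gives one pair of pneumonia rates: 25% untreated and 6% treated with VZIG. Table 2 shows the same pair; its N=81 heads the VZIG-treated column, and the untreated column has no N. On overall enrolment, 8.1 says: "There is no upper or lower limit for the number of patients enrolled".

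**The concern.** The number of patients, power, effect size, test, error rate and planning rates all stand in the protocol, so they should fit together. They do not. Table 4's difference is 19 points, not 25. The protocol does not say whether the 25% is absolute or relative, which control rate it starts from, or whether the test is one- or two-sided. The named test is a two-sample test, yet the untreated group has no denominator.

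This is the protocol's only power statement, and pneumonia is the only efficacy outcome with a planned test; 8.3 treats the others descriptively. A reader who accepts the 80% would take a non-significant result at or near 16 patients as evidence against the product. If VariZIG performs exactly as Table 4 shows for VZIG, that result is the more likely one at 16 patients: 1 − 0.372 = 0.628, about 63%.

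**Working it through.** **Inputs.** n = 16, 80% power and the 25% difference (8.1, Synopsis); Fisher's exact test at 0.05, sidedness not given (8.3); 25% untreated and 6% VZIG-treated (Table 4). The untreated denominator is not given, so control size m is an assumption and is varied below.

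**1. Trying to reproduce the 80%.** Three readings of the sentence were tried.
- *Absolute, 25% to 0%.* Against a fixed 25%, a true rate of 0% always yields 0/16, which is significant (step 2), so power is 100%. With Fisher's test and controls sampled at 25%, two-sided power is 57% at m = 28, 79% at m = 100 and 96% at m = 200; one-sided it is 85% at m = 60.
- *Relative, 25% to 18.75%.* Power against a fixed 25% is P(0/16) = 0.8125^16 = 0.036, about 4%.
- *A 25-point drop from another control rate.* A one-sided, one-sample normal formula at 32% versus 7% gives n = 15.4 and 82% power at 16. But 32% is the top of the 19–32% range in Table 1, not Table 4's 25%, and exact power there is 69%.

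So a figure near 80% can be reached, but only with a true pneumonia rate of zero and an assumed control size, or with a control rate other than Table 4's.

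**2. Rejection region against a fixed 25%, n = 16.**
- P(0 events) = 0.75^16 = 0.0100 (two-sided p = 0.0175): significant.
- P(≤1 event) = 0.0100 + 16 × 0.25 × 0.75^15 = 0.0100 + 0.0535 = 0.0635 (two-sided p = 0.143): not significant.

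Only 0/16 rejects, whether the test is one- or two-sided.

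**3. Power at Table 4's 6%.** 0.94^16 = 0.372, about 37%.

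**4. True rate needed for 80% against a fixed 25%.** Solve (1 − p)^16 = 0.80: p = 1 − 0.80^(1/16) = 0.0138, about 1.4%.

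**5. Fisher's test at 25% versus 6%, controls sampled at 25%.**

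| Assumed m | Two-sided | One-sided |
|---|---|---|
| 28 | 27.1% | 31.3% |
| 60 | 26.9% | 40.5% |
| 100 | 32.0% | 42.8% |
| 200 | 38.9% | 45.6% |

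Smaller control groups do worse: 16.9% two-sided and 21.5% one-sided at m = 16. A one-sample normal approximation gives 35% two-sided and 58% one-sided. Nothing tried at 25% versus 6% reaches 80%.

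**6. Why the missing denominator matters.** With controls observed at exactly 25%, 0/16 gives two-sided Fisher p = 0.101 against 4/16, 0.053 against 5/20, and a significant result once m is 28 or more. The same trial result can pass or fail depending on a number that the protocol does not state.

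**7. Size at which 80% is reached for 6% against a fixed 25%, exact one-sample test.** One-sided at 0.05: first passed at n = 23 (84.3%), below 80% again at 26 to 28, and above it from 29 (90.7%) onward. Two-sided with 0.025 in the lower tail: above 80% from n = 33 (86.6%).

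**The case against.** The strongest reply is that 8.1 claims power for a 25% difference, while the 37% is for 19 points. This is right as far as it goes. A reader might infer that 16 patients can never give 80% power, or that power at a true rate of 0% must be either 0% or 100%. The documents do not support either inference. Fisher's test compares two samples, and if the controls are treated as sampled, an absolute drop from 25% to 0% has about 79% two-sided power at an assumed 100 controls. What remains is that this reading requires no treated patient ever to develop pneumonia, whereas the protocol's only treated rate for this group is 6%.

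A reader might also take 37% as a ceiling for Fisher's test. That holds only when the controls are fixed at exactly 25%; with sampled controls it reaches 45.6% one-sided at m = 200, which is still well short of 80%.

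The remaining objections bear on weight. The primary endpoint is adverse events, and pneumonia is one of several secondary endpoints. Sixteen is a minimum, enrolment has no upper limit, and nothing says that the test will be run at 16. If many more immunocompromised patients enrol, actual power will be higher. All of this stands and lowers the severity, but it does not repair a sentence that ties 80% to 16.

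**Conclusion.** The concern holds in this form: the 25% difference is undefined and conflicts with Table 4, and at Table 4's rates 16 patients do not give 80% power. Against a fixed 25%, power at a true 6% is about 37%. By Fisher's test with sampled controls of assumed size 28 to 200 it is roughly 27% to 46%. Against a fixed 25%, 80% requires a true rate of about 1.4% or lower.

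These figures assume independent patients, a 0.05 level, and that Table 4's 25% and 6% apply to the patients enrolled here. The Fisher range also depends on control sizes that the protocol does not give. The severity is should-fix: the endpoint is secondary and 16 is a floor, but the protocol's only power figure is not supported by its own rates.

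**What to change.** **Section 8.1 and the Synopsis.** Define the difference by stating the control rate, the treated rate and the sidedness. Replace the 80% claim with wording such as: *With 16 patients, power is about 37% if the true pneumonia rate is 6% against a fixed 25%, and 80% only if the true rate is about 1.4% or lower.* Optionally add that exact one-sample power against 6% stays above 80% from about 29 patients (one-sided 0.05, first passed at 23) or 33 (two-sided 0.05).

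**Section 8.3.** Choose one of two routes. Either add the untreated numerator and denominator to Table 4, so that the planned Fisher's test can be run and checked, or test against the fixed 25% with an exact one-sample binomial test and an exact confidence interval. Both are acceptable; Fisher's test need not be dropped if the counts are supplied. Say that the comparison uses all eligible immunocompromised patients.

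**Section 3.3.** No change is needed, since it only refers to 8.1.

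**Cost.** A revised sentence in two places and a clarification in 8.3. No additional enrolment is required. The stated power becomes less favourable.
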